**Fig 1 pone.0325490.g001:**
[figure not shown]
The map of the two study areas in KwaZulu-Natal province in South Africa. The white polygon in the South Africa map shows the Lesotho country. The map was created using ArcGIS Pro software version 3.4.0 supported by Esri. The basemap (e.g., map data and shapefiles) were derived from the United Nations Office for the Coordination of Humanitarian Affairs, Humanitarian Data Exchange (https://data.humdata.org/dataset/cod-ab-zaf).

More detailed information concerning the study design for each study objective is provided in the following paragraphs.

#### Objective 1. Understanding the impact of floods on healthcare utilisation, lives and livelihoods (March 2025–September 2025).

To understand the impacts of the floods on PLHIV, we will conduct semi-structured in-depth interviews (IDIs) and focus group discussions (FGDs) across the two study sites. Interview questions will cover topics around how PLHIV make sense of their experience of the April 2022 KZN floods – especially for the unexposed population, while the unexposed population (in Somkhele) will explore participants’ views about the 2022 KZN floods and other floods and EWEs experienced in their contexts. The interviews and FGDs will explore how PLHIV were impacted by the floods, including their health, healthcare access and utilisation and livelihood sustenance. We will also interview key informants from health and health-determining sectors, including the Department of Health, Department of Social Development, and Disaster Management Agency, to gain an understanding of actions or inactions towards mitigating the impact of the floods.

#### Objective 2. Measuring the economic losses and healthcare related costs (March 2025–December 2025).

We will follow the recommended methods to identify and evaluate the impacts of socioeconomic factors associated with floods and measure the economic impacts and losses, including healthcare utilisation and related costs, attributable to recent floods for a randomly selected sample of PLHIV. The study design, analytical methods and reporting of the findings will follow the Consolidated Health Economic Evaluation Reporting Standards (CHEERS) Statement [43].

We will evaluate the economic burdens of floods in terms of direct and indirect costs (e.g., healthcare resources utilisation and work productivity loss). Individual-level data will be collected via structured questionnaires. A micro-costing approach (including a bottom-up construction of costs) will be employed to estimate costs associated with healthcare utilisation and other economic impacts of floods. The overall costs incurred due to floods will be estimated from a provider perspective (and a patient perspective, where data permits). We also collect socioeconomic and demographic information (e.g., age, gender, employment status, etc) of the study participants.

#### Objective 3. Co-development and co-prioritisation of policy actions (May 2025–May 2026).

In this objective, we will adopt a mixed-methods approach involving both quantitative and qualitative data collected through existing data sources, as well as engagements and workshops with key stakeholders involved in the care of PLHIV and those directly affected by the floods. This objective will be achieved through two main phases, as described below.

Phase 1: To identify early adaptive policy actions to minimise the health, economic and social impacts of floods on PLHIV

Phase 2: To create a priority list of early actions identified in Phase 1.

In phase 1, we will use the adapted Participatory Impact Pathways Analysis (PIPA) approach developed by the University of Sussex following the STEPS Centre [44,45]. PIPA provides a ‘road map’ that supports the co-development of a list of policy interventions by consulting and including multiple key stakeholders (e.g., patient representative, policymaker, health provider, etc). This approach is designed for complex contexts and provides a framework for ‘action research’ on processes of change. It has been successfully applied for co-production purposes in climate change research [45,46]. PIPA is a planning and, monitoring and evaluation tool designed to assist the people involved in a project, programme or organisation and make explicit their theories of change (i.e., how they see themselves achieving their goals and having an impact). Climate risk narratives are stories describing a subset of plausible – yet certainly not definitive – futures within the spread of climate projections intertwined with local context, impacts and vulnerabilities. Climate risk narratives enable the input of multi-model future climate scenarios into the project for exploring the health risks of future floods in PLHIV.

In phase 2, in line with the World Health Organization’s good practice for priority-setting [47–50], a multi-criteria decision analysis (MCDA)-based framework will be developed and implemented to rate, rank and prioritise the policy actions identified in phase 1 to support evidence-based climate change adaptation policymaking (particularly for flooding) involving key stakeholders and partners from all relevant sectors mentioned above via a workshop.

### Ethics and consent to participate

Ethical approvals for this study have been obtained from the University of Sussex, Brighton and Sussex Medical School Research Governance Ethics Committee (ER/BSMS9P2V/2/1) in the UK and the University of Kwazulu-Natal Biomedical Research Ethics Committee (BREC/00006821/2024) in South Africa. Participation in the study will be voluntary. All participants will sign a written informed consent form for participation and be given information that participation is voluntary and that they can withdraw from the study at any time.

### Overview of participant recruitment and inclusion criteria

We will recruit PLHIV in the Hlabisa subdistrict through a randomisation process. Potential participants will be randomly drawn from – and recruited – through the AHRI Health and Demographic Surveillance System (HDSS) [39]. In this programme, triannual household-based surveys are used to collect sociodemographic data from approximately 150,000 people in an 845km^2^ area coupled with annual home-based, point-of-care HIV testing, linked to real-time HIV clinical data and health service utilisation records from all 11 regional primary healthcare clinics that provide HIV care, hospitalisation data at the single district referral hospital, and annually death data carried out through verbal autopsies of all deaths in the catchment area. This research database will be used as a sampling frame to randomly select and invite PLHIV to take part in the study in Hlabisa.

AHRI does not have a similar research infrastructure in Ndwedwe, iLembe district. To identify PLHIV in the community without stigmatising them, we will hold monthly meetings with the community engagement department (CED) at AHRI to engage the health facilities and traditional structures in Ndwedwe as part of the community entry process, trust building and stakeholder engagement. Part of this process will entail a series of road shows and edutainment programmes – led by the CED – encapsulating games and educational talks on climate change and health to sensitise the community about the study. Subsequently, the study team will work closely with community caregivers and community-based organisations who have access to PLHIV to facilitate recruitment. Individuals who are recruited through this process will be informed about the study and offered participation if they meet the eligibility criteria. Although it is logistically easier to recruit PLHIV from healthcare facilities, this will introduce selection bias as it means only PLHIV who are still able to access healthcare facilities will be offered participation in the study, and these individuals may differ from the general population of PLHIV in Ndwedwe.

Participants will be recruited if (a) they are aged 18 years and over, (b) they were diagnosed with HIV before the April 2022 floods, (c) were on antiretroviral therapy before April 2022, (d) were resident in Ndwedwe (exposed group) or Hlabisa (unexposed group) over a month before and during April 2022, (e) were present for and remember the April 2022 floods (for the exposed group), and (f) they are able to give written consent.

More detailed data regarding the study participants and sample size for each study objective is provided in the following sections.

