#### Objective 2. Measuring the economic losses and healthcare related costs.

The background loss from care after 12 months of antiretroviral treatment ranges from 20–30% [51]. Therefore, we will need to recruit a total of 424 PLHIV (212 unexposed and 212 exposed individuals) at a matched exposed-unexposed ratio of 1:1 (one unexposed for one exposed) to reach an 80% power at 0.05 significance level to detect a 90% increase in odds of loss from care during the first 6 months following the floods. Although we do not aim to estimate loss from care (i.e., loss from follow-up) in this study, it underpins our study hypothesis while not the primary reason for this study. The AHRI HDSS databases described in the participant recruitment section will serve as the sampling frame for randomly selecting the 212 unexposed individuals in Hlabisa, of whom 70% will be female, which is representative of the proportion of females amongst all PLHIV who engage with the surveillance programme. A similar approach will be taken to recruit 212 exposed PLHIV in Ndwedwe by working closely with AHRI CED, community caregivers and other community-based organisations, as mentioned above.

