## Discussion

The present study aims to evaluate and understand the social and economic impacts (including coping strategies, access to care, healthcare service utilisation and associated costs, work productivity losses and other socioeconomic instabilities) of the recent floods among PLHIV in rural South Africa and use participatory research methods and MCDA to co-design and co-rank a list of policy action interventions. To the best of our knowledge, this study is the first study to use this particular mixed-methods approach to provide an in-depth analysis of the social and economic pathways for how climate-induced extreme events, such as floods, are likely to affect vulnerable communities such as PLHIV.

South Africa is prone to climate-driven EWEs. In 2015, KZN experienced one of the worst droughts recorded in the country, which resulted in the declaration of a state of disaster [67]. Orievulu et al. (2022) investigated the impact of drought on HIV treatment and care elucidating mechanistic pathways that implicated food insecurity and productivity loss in the context of pervasive poverty that was gendered [25,68]. The April 2022 floods in KZN, also the province most impacted during the 2015 droughts, resulted in hundreds of deaths, damage to infrastructure and disruption of services, including healthcare. Over 40,000 people were displaced because of the floods, many of whom are still homeless [29,69]. KZN is the epicentre of the HIV epidemic in South Africa, with more than one-third of the adult population living with HIV [39]. The impact of EWEs, such as floods, can result in acute interruption of treatment and care in PLHIV [25,68], and competing livelihood priorities could mean that some of these individuals may not return to care, resulting in chronic disengagement and associated increase in morbidity, loss of income and mortality.

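### Objective 2 describes its sample as randomly selected and matched, but only Hlabisa is drawn at random; sampling method is fully confounded with flood exposure

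*Protocol article*

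**What the plan says.** Three statements in the protocol article present the Objective 2 sample as one random, matched design:

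- The Objective 2 design section sets out to measure losses "attributable to recent floods for a randomly selected sample of PLHIV", with no distinction between sites.
- The Objective 2 sample size section fixes 212 per group "at a matched exposed-unexposed ratio of 1:1 (one unexposed for one exposed". It names no matching variable. The only composition figure is a 70% female share, given for Hlabisa.
- The same section then says: "A similar approach will be taken to recruit 212 exposed PLHIV in Ndwedwe by working closely with AHRI CED, community caregivers".

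The section on recruitment and inclusion criteria describes two different routes:

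- Hlabisa: "This research database will be used as a sampling frame to randomly select and invite PLHIV to take part in the study in Hlabisa".
- Ndwedwe: "AHRI does not have a similar research infrastructure in Ndwedwe, iLembe district". There, community engagement and road shows come first, and then "the study team will work closely with community caregivers and community-based organisations who have access to PLHIV to facilitate recruitment". Eligible people found this way are offered participation.

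The same section avoids clinic recruitment in Ndwedwe because it would reach only people who can still get to a facility, and these may differ from other PLHIV in the area. The Objective 2 analysis section plans adjustment for baseline covariates such as age and gender, multiple imputation for missing data, and bootstrapping.

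**The concern.** A draw from a population register and recruitment through intermediaries are not similar approaches. Each site uses only one of them, so any difference between the groups mixes the effect of the flood with the effect of how people were found.

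The plan's own argument against clinics applies here too. People in contact with a caregiver or an organisation may differ from other PLHIV, just as people in contact with a clinic may. The plan does not carry the argument over.

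The planned analysis does not repair this. Contact with services and severity of flood impact lie close to the outcomes themselves (healthcare use, costs, lost work), and age and gender are weak proxies for them. Imputation deals with gaps among participants, not with people who were never recruited. Similar area profiles say nothing about who is sampled within each area, and a larger sample leaves the bias as it is. The main quantitative contrast of the study is at stake.

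**Working it through.** **1. The plan's own sample size.** Inputs from the Objective 2 sample size section: background loss from care 20–30%, odds ratio (OR) 1.9, power 80%, significance level 0.05 (two-sided assumed), 1:1.

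- At a background risk of 0.20, the odds are 0.20/0.80 = 0.25. The exposed odds are 1.9 × 0.25 = 0.475, so the exposed risk is 0.475/1.475 = 0.322.
- Log odds ratio formula: n = (1.96 + 0.84)² × [1/(0.20 × 0.80) + 1/(0.322 × 0.678)] / (ln 1.9)² = 207 per group.
- The continuity-corrected formula for two proportions gives 219 at 0.20 and exactly 212 at 0.21.
- With 212 per group and a background risk of 0.20, power is 82%.

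The figure of 212 is therefore consistent with the plan's inputs at the low end of its range, and the arithmetic is not the problem. Formulas for independent groups are enough to reach it. A McNemar calculation gives 205 pairs if pairs are uncorrelated and 186 at a within-pair correlation of 0.1, so 212 shows no gain from pairing. All these formulas assume that each group represents its source population.

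**2. The stated properties against the described procedure.**

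| Property | Hlabisa | Ndwedwe |
|---|---|---|
| Sampling frame | Surveillance database | None described |
| Random step | Yes | None described |
| Route to the participant | Invitation after the draw | Engagement, caregivers, organisations |
| Must have been present for and remember the floods | Not required | Required |
| Matching variable | None named | None named |

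**3. What differential selection would do.** Within a site, let r be the probability of being recruited if lost from care, divided by that probability if still in care. The odds in the sample are r times the odds in the population. Hence

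observed OR = true OR × (r_exposed / r_unexposed).

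The document gives no value for either r, so the ratios below are assumptions. The last two columns give the probability of a significant excess with 212 per group, holding the observed Hlabisa risk at 20% or 30%.

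| True OR | Ratio | Observed OR | At 20% | At 30% |
|---|---|---|---|---|
| 1.9 | 1.0 | 1.90 | 82% | 89% |
| 1.9 | 0.9 | 1.71 | 66% | 75% |
| 1.9 | 0.75 | 1.43 | 33% | 41% |
| 1.9 | 0.5 | 0.95 | – | – |
| 1.0 | 1.25 | 1.25 | 16% | 19% |
| 1.0 | 1.5 | 1.50 | 42% | 51% |

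The apparent effect vanishes at a ratio of 1/1.9 = 0.53. Without any selection, a true OR of 1.0 gives a significant excess 2.5% of the time.

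**The case against.** **The constraint is disclosed.** The article says that Ndwedwe has no comparable infrastructure, gives avoidance of stigma as a reason for the route, and rejects clinics because of selection bias. It is also a condensed account, so lists or tracing logs may exist in the full protocol. This stands as a defence of the route. It does not defend calling the sample random or the approach similar.

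**Matched may mean only the 1:1 ratio.** The parenthesis in the sample size section allows that reading. A reader might infer that matching will not be done; the article does not show this, only that no variable is named. The word is unclear rather than proven false.

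**Selection in the exposed group only.** A reader might infer that selection acts on the exposed alone, so that the OR shrinks by r_exposed. The document does not support this. Hlabisa participants must also have survived to 2025, be traced and agree, and the 70% female share is benchmarked on people who engage with the surveillance programme. They are interviewed at a fixed office, while the exposed may agree another place. Only the ratio of the two selection factors matters: with 0.75 in Ndwedwe and 0.9 in Hlabisa it is 0.83 and the observed OR is 1.58; if the two are equal, it stays 1.9.

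**A hidden effect as the likely result.** It is tempting to argue that the worst affected are the hardest to find, and to cite the Discussion: "Over 40,000 people were displaced because of the floods, many of whom are still homeless". That figure is for the KwaZulu-Natal floods as a whole, not for Ndwedwe. Road shows on climate and health could equally draw in the worst affected. The text also does not say that caregivers reach only people still in care.

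**Loss from care is not a study outcome.** The sample size section says that the study does not aim to estimate it. The figures above illustrate a mechanism that applies equally to costs and productivity, but they do not size the bias there.

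**Conclusion.** The contradiction is in the text. The design section claims random selection for the whole Objective 2 sample and the sample size section claims a similar approach, while the recruitment section describes a random draw for one site only. Sampling method and exposure cannot be separated, and the planned covariate adjustment does not change that.

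The consequence can go either way. Under assumed selection ratios from 0.5 to 1.5, the distortion runs from wiping out an OR of 1.9 to producing an OR of 1.5 from nothing. These numbers rest on assumed ratios and on the sizing outcome; direction and actual size cannot be determined from the document. The point should be fixed. It does not show that the study is invalid or that its result will be biased towards no effect.

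**What to change.** 1. Describe Ndwedwe as a non-probability sample. Remove the claims of random selection and of a similar approach for that site.
2. Recruit Ndwedwe first, or in parallel batches. Then draw Hlabisa at random from the surveillance database, frequency-matched on age band, sex and duration of antiretroviral treatment, and keep these factors in the model. The fixed 70% female share for Hlabisa would then have to follow the Ndwedwe distribution. Otherwise delete the word matched. Matching balances these factors only; it does not remove selection on contact with services, so step 3 is needed as well.
3. At both sites, log recruitment source and the numbers approached, untraceable, moved, dead and refused, as far as known. Prespecify a sensitivity analysis over r_exposed/r_unexposed with values both below and above 1.
4. Record the recruiting caregiver or organisation for each exposed participant and resample by it in the bootstrap already planned, since people who share a recruiter may resemble each other.

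Sampling at random from coded caregiver client lists would be stronger, but it is optional. It covers only caregivers' clients, must not create stigma or consent problems, and cannot yield 212 interviews from 212 draws if the lists include people who have died.

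Cost: a later start to Objective 2 in Hlabisa, some record-keeping, possibly wider intervals, and a less favourable description of the sample. According to the data collection section, Objective 2 data are collected after the preliminary qualitative analysis, so the plan leaves room for these changes.

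### The ART eligibility criterion is not anchored to flood onset, so people already out of care can enter and distort the HIV-care comparisons (not the economic ones)

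*Protocol article*

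**What the plan says.** The eligibility list in the protocol article (Overview of participant recruitment and inclusion criteria) requires under (c) that participants "were on antiretroviral therapy before April 2022". It gives no look-back window and does not ask that treatment was continuing when the floods began. The next criterion, (d), does fix the period for residence: "over a month before and during April 2022".

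The same section describes two recruitment routes. Hlabisa (unexposed) draws at random from a surveillance database linked to HIV clinical records. Ndwedwe (exposed) has no such infrastructure and recruits through community caregivers and community organisations, deliberately avoiding clinic-only recruitment so that people who no longer reach facilities are not missed.

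Under Sample size, Objective 2, the study is sized on loss from care: "The background loss from care after 12 months of antiretroviral treatment ranges from" 20% to 30%, and each group is to have 212 people for power of 80% with a 5% test. The stated target is "to detect a 90% increase in odds of loss from care during the first 6 months following the floods". The same paragraph says that loss from care is not itself to be estimated, although it underpins the hypothesis. The Abstract lists adherence and healthcare use among the outcomes, alongside out-of-pocket expenses, coping, productivity loss and other economic losses.

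**The concern.** A person who stopped ART in, say, 2020 meets criterion (c) as written. That person cannot be lost from HIV care because of the April 2022 floods and has no ART course for the floods to interrupt. In any comparison of HIV-care disruption, such people add either events unrelated to the flood or structural non-events.

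Two things are at stake. If both groups hold the same share of earlier leavers, the exposed–unexposed contrast in HIV-care outcomes moves toward the null. If the shares differ, the contrast is biased, and a larger sample does not help. Different shares are plausible because the two groups are found by different routes. The Ndwedwe route in particular is meant to reach people outside clinics, and without status at onset it cannot separate those who left because of the floods from those who left before them.

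**Working it through.** **Inputs from the protocol article (Sample size, Objective 2).** 212 per group, 1:1; odds ratio (OR) 1.9; power 80%; significance level 0.05 (sidedness not stated, two-sided assumed); background loss p0 of 20–30% (no single planning value stated).

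**Input not in the documents.** The share f of participants already off ART or out of care at flood onset. Assumed range: 5–30%.

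**Step 1: reproduce the sample size.** With p0 = 0.20, p1 = p0·OR/(1 − p0 + p0·OR) = 0.38/1.18 = 0.322. On the log-odds-ratio scale, n per group = (1.960 + 0.842)² × [1/(p0(1−p0)) + 1/(p1(1−p1))]/(ln 1.9)² = 7.849 × (6.250 + 4.580)/0.412 ≈ 207. Other formulas at p0 = 0.20 give 203 (pooled two proportions), 205 (matched pairs, no within-pair correlation) and 219 (continuity-corrected; exactly 212 at p0 = 0.21). With 212 per group, pooled two-proportion power is 0.818 at p0 = 0.20. At p0 = 0.30, p1 = 0.57/1.27 = 0.449 and power is 0.889. The plan's figure therefore fits the 20% end of its range, with everyone at risk.

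**Step 2: the same share f in both groups.** There are two ways to count earlier leavers:
- A, counted as lost: p′ = f + (1 − f)p.
- B, counted as not newly lost: p′ = (1 − f)p.

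Example with f = 0.20, p0 = 0.20. A: 0.360 v 0.458, OR 1.50, power 0.534. B: 0.160 v 0.258, OR 1.82, power 0.697.

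| p0 | f | A: OR | A: power | B: OR | B: power |
|---|---|---|---|---|---|
| 0.20 | 0 | 1.90 | 0.818 | 1.90 | 0.818 |
| 0.20 | 5% | 1.75 | 0.744 | 1.88 | 0.791 |
| 0.20 | 10% | 1.64 | 0.670 | 1.86 | 0.762 |
| 0.20 | 20% | 1.50 | 0.534 | 1.82 | 0.697 |
| 0.20 | 30% | 1.41 | 0.420 | 1.79 | 0.625 |
| 0.30 | 0 | 1.90 | 0.889 | 1.90 | 0.889 |
| 0.30 | 5% | 1.81 | 0.845 | 1.86 | 0.863 |
| 0.30 | 10% | 1.73 | 0.796 | 1.83 | 0.833 |
| 0.30 | 20% | 1.61 | 0.690 | 1.77 | 0.765 |
| 0.30 | 30% | 1.53 | 0.580 | 1.72 | 0.685 |

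**Step 3: unequal shares, p0 = 0.20.**
- No flood effect, f = 10% in Hlabisa and 20% in Ndwedwe, rule A: 0.10 + 0.90 × 0.20 = 0.28 v 0.20 + 0.80 × 0.20 = 0.36. OR = (0.36/0.64)/(0.28/0.72) = 1.45, an effect that does not exist.
- The same shares under rule B: 0.90 × 0.20 = 0.18 v 0.80 × 0.20 = 0.16. OR = (0.16/0.84)/(0.18/0.82) = 0.87, an error the other way.
- Shares reversed, true OR 1.9, rule A: 0.36 v 0.10 + 0.90 × 0.322 = 0.390. OR = (0.390/0.610)/(0.36/0.64) ≈ 1.14, most of the effect hidden.

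**Step 4: restrict to people in care at onset.** The OR returns to 1.90 whatever f is, and n falls to 212(1 − f). For f = 5, 10, 20 and 30%, power is 0.799, 0.777, 0.727 and 0.669 at p0 = 0.20, and 0.873, 0.855, 0.811 and 0.757 at p0 = 0.30. At each f this exceeds both A and B.

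**The case against.** Several points on the other side have force.

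- **Wording.** The criterion can be read as being established on ART when the floods arrived, and a fuller protocol that is not shown may say so. This stands as a possibility. But eligibility is set out here as a complete lettered list, residence in the same list is anchored, and two teams using different routes have to apply the phrase. An ambiguity they could resolve differently is worth removing.
- **Outcomes.** A reader might infer that people already out of care cannot show any flood-related disruption. The documents do not support that. Someone off ART can still lose wages or assets, pay out of pocket or change how they cope, and these losses are the core of Objective 2. The point is limited to HIV-care outcomes.
- **Planned analysis.** The power figures concern loss from care, which the article says will not be estimated. This stands: the figures show the size of the mechanism and are not the power of a planned test. No such figure is available for adherence or costs.
- **The share.** A reader might take the article's 20–30% as the share out of care in April 2022. It is loss after 12 months of treatment, and the share at flood onset is not given. Hence the assumed range.
- **Counting rule.** Counting earlier leavers as lost sits badly with an event defined over the six months after the floods. Rule B is closer to that definition and gives the milder loss, so both are shown.
- **Direction.** Dilution is not certain. With unequal shares the bias can go either way, and the documents do not say which.
- **Exclusion as a remedy.** Screening from clinical records in Hlabisa and from self-report in Ndwedwe could itself create an imbalance, and would discard people who are informative for the economic outcomes. This stands and has shaped the fix.

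**Conclusion.** The point holds in a limited form. Criterion (c) leaves treatment status at flood onset undefined, and for adherence, HIV healthcare use and the sizing hypothesis that allows people who are not at risk into both groups. Assuming an equal share of 5–30%, power for the sizing contrast falls from 0.82 to 0.74–0.42 (counted as lost) or 0.79–0.63 (counted as not newly lost) at 20% background risk. At 30% background it falls from 0.89 to 0.85–0.58 or 0.86–0.69. With unequal shares, a difference of 10% against 20% is enough to produce an OR of 1.45 or 0.87 when the floods have no effect, depending on the counting rule.

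These results rest on an assumed share, a two-sided test, an unmatched calculation and an outcome that the study does not plan to estimate. They do not show that the study as a whole is underpowered, and they say nothing against the productivity, cost or coping comparisons.

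**What to change.** Define being on ART and in care at flood onset, for example by a clinic visit or treatment supply covering March 2022, and state whether criterion (c) also admits people who had stopped by then. Record this status with the same questionnaire item at both sites. Use Hlabisa's linked records only to check how well that item performs, not to classify people there by a different standard.

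Restrict the adherence and HIV-care disruption analyses to participants who were on ART at onset. Keep all participants for the economic, productivity and coping outcomes. Report the share not in care at onset by site, so that any imbalance between the recruitment routes is visible.

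The cost is one added question. According to Data collection, Objective 2, the questionnaire is still to be finalised and piloted. The answer relies on about three years' recall, since Objective 2 is scheduled for March to December 2025. The care-disruption analyses use fewer people: at an assumed 20%, about 170 per group (212 × 0.80), with the power shown in step 4. If 212 in-care participants per group are wanted, 212/0.80 = 265 would have to be recruited.
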